**3. Scientific Background of study**

Endoscopic ultrasound-guided fine-needle aspiration (EUS-FNA) is an accurate and sensitive tool for pancreatic solid mass diagnosis, involving few major adverse events [1]. In general, EUS-FNA has an essential role in establishing exact diagnoses and therapeutic strategies for pancreatic solid masses; this method has a high but wide range of sensitivity and specificity (75% to 92% and 82% to 100%, respectively), with an accuracy and incidence of adverse events ranging from 70% to 100% and 0% to 3%, respectively [2-4].

Its usefulness, however, is limited for the following reasons. First, the diagnostic yield of smear cytology with EUS-FNA is largely dependent on the availability of a cytopathologist, and the NPV of the procedure is very low; in other words, FNA findings negative for pancreatic solid masses do not reliably rule out the possibility of pancreatic malignancies [5]. Second, it is hard to discriminate between inflammatory regenerative tissue and well-differentiated neoplasm based only on cytological specimens. In addition, histological analysis of tissue architecture or immunohistochemical staining may be necessary for accurate diagnosis of pancreatic lymphoma or neuroendocrine tumors [6,7]. Furthermore, in the current personalized medicine era, it is becoming increasingly essential to obtain histological tissue for molecular analysis. Therefore, there is a clear need for alternative techniques to improve the diagnostic performance of EUS-guided tissue sampling; an EUS-fine needle biopsy (FNB) device has recently been developed to enable retrieval of optimal core specimens for histologic analysis. Recent studies have reported EUS-FNB to be a feasible, safe, and effective technique for obtaining histological core samples for diagnosis of benign and malignant diseases as well as for staging workup in gastrointestinal malignancies [8,9].

Similar to EUS-FNA the feasibility and diagnostic yield of EUS-FNB depends on the location, size, and characteristics of target lesions in addition to technical and procedural factors (needle diameter and handling technique, material processing and expertise, and training and interaction between endosonographers and cytopathologists). Furthermore, technical limitations such as mechanical friction of the needle-firing mechanism in larger-caliber needles in the torqued trans-duodenal position, when applied to pancreatic head or uncinated process lesions, may occur with EUS-FNB [10-13]. For this reason, a similarly designed but more flexible FNB device has been developed using a 25-gauge needle platform [14]. Approximately 60% to 70% of diagnosed ductal adenocarcinomas occur in the pancreatic head or uncinated process, underscoring the need for an effective trans-duodenal approach. Furthermore, blood and cellular debris contamination complicate cytopathological interpretation, a common occurrence with the widely used 22-gauge needle.[15] In addition, it is often difficult to penetrate a calcified solid mass with a 22-gauge needle.[15] We hypothesized that a 25-gauge needle would provide an appropriate specimen while more easily penetrating solid pancreatic masses.

However, it is unclear whether the theoretical benefit of 25-gauge needles for EUS-FNB actually results in a higher procurement rate of high-quality histologic core samples compared to 22-gauge needles. Furthermore, no study has evaluated histologic core procurement rates of 25-gauge needles. Therefore, the aim of this study was to compare the efficacy of the recently developed 25-gauge EUS-FNB device to 22-gauge EUS-FNB for obtaining histologic core tissues in order to assess solid pancreatic masses.

[figure not shown]

Figure 1. 25-gauge Ultrasound biopsy needle (EchoTip® ProCore™ High Definition Ultrasound Biopsy Needle, Cook Medical Inc, Bloomington, IN)

Figure 2.

**4. Summary of study design**

**Study design:** Single center, prospective, randomized, double-blinded corss-over study

**Study participants:** Planned number: set at 66 pairs

**Study centers:** Severance Hospital, Yonsei University College of Medicine, Seoul, Korea

**Evaluated diagnostic**

**procedure:** Endoscopic ultrasound-guided fine-needle biopsy (EUS-FNB) of pancreatic mass lesions

**5. Sample size calculation**

To calculate the sample size, we referred to the recent studies[19,21] using the same needle calibers as ours (EUS-FNB with the 25-gauge and 22-gauge needles). In the first study[19] conducted by Bang et al, proportion (%) of optimal histologic core using 22-gauge FNB needle was 70% and proportion (%) of optimal histologic core using 25-gauge FNB needle was 92% in second study[21] cuducted by Iwashita et al. A sample size of 56 pairs achieves 80% power to detect an odds ratio of 4.929 using a two-sided McNemar test with a significance level of 0.05. The odds ratio is equivalent to a difference between two paired proportions of 0.276. Assuming a 15% dropout rate, the final sample size was set at 66 pairs.

**6. Inclusion criteria**

suspected solid pancreatic masses based on clinical work up and image modality that required cytopathological confirmation.

**7. Exclusion criteria:**

(a) cystic pancreatic lesions without the evidence of solid component suspected with malignant transformation

(b) hemodynamical instability

(c) severe coagulopathy (international normalized ratio > 1.5 or platelet count < 50,000 cells/cubic millimeter [cmm^3^])

(d) inability to suspend antithrombotic therapy

(e) pregnancy

(f) refusal to provide informed consent or participate in the study

**8. Methods of screening**

Medical record, History, Physical exam, Vital sign, CBC, blood chemistry including serum amylase and lipase, abdominal computed tomography (CT) scans, Pancreato-biliary MR

**9. Standard diagnostic modality of study**

EUS-FNA with aspiration 22-gauge needle has an essential role in establishing exact diagnoses and therapeutic strategies for pancreatic solid masses; this method has a high but wide range of sensitivity and specificity (75% to 92% and 82% to 100%, respectively), with an accuracy and incidence of adverse events ranging from 70% to 100% and 0% to 3%, respectively.

**10. Study procedure**

This study will be a randomized, double-blinded, prospective study of 66 consecutive patients with pancreatic solid masses who will be referred to our medical center for EUS-FNB during 1 year after IRB approval in Severance hospital. Patients will be eligible for the study based on the following criteria: suspected solid pancreatic masses based on clinical work up and image modality that required cytopathological confirmation. Exclusion criteria will include: (a) cystic pancreatic lesions without the evidence of solid component suspected with malignant transformation; (b) hemodynamical instability; (c) severe coagulopathy (international normalized ratio > 1.5 or platelet count < 50,000 cells/cubic millimeter [cmm^3^]); (d) inability to suspend antithrombotic therapy; (e) pregnancy; and (f) refusal to provide informed consent or participate in the study. All patients will undergo EUS-FNB under moderate-to-deep balanced propofol sedation based on midazolam according to current guidelines [16]. Patients will be monitored for immediate post-procedural adverse events for least 4 hours after completion of the procedure and will be followed up for up to 30 days to detect late adverse events; non-surgical patients received clinical follow-ups for at least 6 months.

All patients will undergo EUS-FNB with 22-gauge (Echotip ProCore; Cook Endoscopy Inc, Limerick, Ireland) and 25-gauge (Echotip ProCore; Cook Endoscopy Inc, Limerick, Ireland) needles subsequently for the same pancreatic lesion; the procedures will be performed by an experienced echoendoscopist ([name]) with a current volume of 750 EUS cases per year, including 150 or more FNA/FNB, using a well-established technique [17]. The FNB device will be made of a 140-cm stainless steel with a 5.2 F shaft ending with a beveled tip 4 mm in length within a spiral steel sheath surrounded by a Teflon cover. All procedures will be performed with a linear array echoendoscope (Olympus UCT 260, Olympus Co., Tokyo, Japan). After visualizing the target lesion in the endosonographic plane, the echoendoscopist will use color Doppler to identify the optimal position for puncture without intervening vessels between the needle and target lesion. The needle will be inserted into the target tissue under EUS guidance via the duodenum for pancreatic head and uncinate masses and via the stomach for pancreatic body and tail masses. Once the lesions will be well penetrated with the needle, the stylet will be removed; a 10-cm^3^ suction syringe will be applied to the needle hub, and 10 uniform back-and-forth movements will be performed within the lesion during each needle passage. The needle will be then withdrawn into the spiral steel sheath and detached from the echoendoscope. After two individual punctures, the first needle will be withdrawn into the catheter and removed; the procedure will be repeated in same fashion with the second needle. The FNB needle sequences will be randomly assigned in a 1:1 proportion based on a computer-generated random order (22- or 25-gauge first), and two punctures will be conducted for each needle respectively. The allocation sequence will be concealed using opaque sealed envelopes, and neither the cytopathologist nor the patients will be unaware of the treatment allocation.

Tissue samples obtained from the first passage by advancing the stylet within the first needle assembly will be immediately smeared onto slides, fixed in a 95% ethanol solution, and will staine using the Papanicolaou method for cytological analysis. Tissue samples from the second passage of the first needle will be recovered in formalin for histological analysis using the same advancing method. One cytopathologist ([name]), experienced in gastrointestinal cytology and blinded to the type and needle sequence, will obtaine the tissue samples and view all prepared slides. The final cytological results will be classified into 4 diagnostic categories (a) positive for malignancy, (b) suspicious for malignancy, (c) negative for malignancy, and (d) non-diagnostic as Table 1 [18].

A final confirmed diagnosis of benign or malignant disease will be according to the following reference methods: (a) definite benign or malignant pathological diagnosis based on analysis of surgically resected specimens from operated patients, (b) disease-specific death, and (c) no signs of disease progression or regression during the 6 month or longer follow-up periods according to clinical course or image modality used for suspected pancreatic inflammation at the time of the procedure.

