**13. Statistical analysis**

Descriptive statistics were provided for binary and continuous variables using incidence frequency (%) and mean ± standard deviation and range. McNemar tests were used to compare binary variables, and two-sample *t*-tests were used to compare continuous variables. Sensitivity, specificity, diagnostic accuracy, positive predictive value (PPV), and negative predictive value (NPV) of each needle were calculated based on per protocol analysis. Two-sided *P*-values were calculated and significance was accepted at 5%. All statistical analyses were performed using PASW Windows, version 18.0.0 (SPSS Inc., Chicago, IL, USA).

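### The reference standard gives no malignant route for an unresected patient alive at follow-up, and no benign route for an unresected mass not suspected to be inflammation at entry

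*Protocol*

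**What the plan says.** Section 10 (Study procedure) of the protocol states that the final diagnosis of benign or malignant disease follows three reference methods.

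- Surgery and death, the first two: "a) definite benign or malignant pathological diagnosis based on analysis of surgically resected specimens from operated patients, (b) disease-specific death". The second has no time limit.
- Follow-up, the third: "c) no signs of disease progression or regression during the 6 month or longer follow-up periods according to clinical course or image modality", with the qualifier "used for suspected pancreatic inflammation at the time of the procedure".

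The list has no residual category. The same section provides for patients who are not operated on: "non-surgical patients received clinical follow-ups for at least 6 months". Section 15 lists, among the variables to record, operability and a reference diagnosis with clinical and pathological elements, but gives no rule for the clinical part.

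Section 13 (Statistical analysis) uses the result: "Sensitivity, specificity, diagnostic accuracy, positive predictive value (PPV), and negative predictive value (NPV) of each needle were calculated based on per protocol analysis". It does not say what happens to a patient without a reference diagnosis. Section 12 makes diagnostic performance a secondary goal.

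**The concern.** Two groups of patients fit none of the three methods.

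1. An unresected patient who is alive at follow-up with a progressing or metastatic mass. Surgery and death do not apply, and the follow-up method requires the absence of progression, so it can only confirm benign disease.
2. An unresected patient whose mass was thought malignant at entry but proves benign over time. The follow-up method is limited to suspected inflammation.

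The protocol foresees non-surgical patients and follows them for at least 6 months, but what that follow-up shows about malignancy is not among the listed methods.

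A patient without a reference diagnosis cannot be placed in the two-by-two table of either needle. At stake are the precision of sensitivity and the meaning of the predictive values, since the malignant patients who remain are those who were resected or who died of disease. If the gap were instead filled by taking a positive trial biopsy as the diagnosis, the test would serve as its own reference, and positive predictive value and specificity would move toward 100%. The protocol does not say that this will be done, but nothing in it rules it out.

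**Working it through.** The protocol states no figure for the reference standard, the share of patients verified, or the accuracy of the two biopsy needles, so there is no figure to reproduce.

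**Inputs**

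- From the protocol: 56 evaluable pairs (section 5). Background sensitivity of 75-92% and specificity of 82-100%, quoted in section 3 for fine-needle aspiration and used here only for illustration.
- Assumed, not in the protocol: 80-90% of patients have cancer; 10-30% of cancers are resected; 20-60% of unresected cancer patients die of disease by follow-up; specificity is 100%.

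**Step 1. Share of cancers without a reference diagnosis**

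Share = (1 - resected) × (1 - dead of disease among the unresected).

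- Lowest: (1 - 0.30) × (1 - 0.60) = 0.28.
- Highest: (1 - 0.10) × (1 - 0.20) = 0.72.

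**Step 2. NPV**

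NPV = TN / (TN + FN), where TN and FN are the true and false negatives. Take 56 patients as 48 cancers and 8 benign, with sensitivity 85%. All patients classified: FN = 48 × 0.15 = 7.2. Half of the cancers unclassified, independently of the needle result: FN = 24 × 0.15 = 3.6.

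| Patients lost | NPV |
|---|---|
| None | 8 / (8 + 7.2) = 8/15.2 = 53% |
| Half of cancers, no benign | 8 / (8 + 3.6) = 8/11.6 = 69% |
| Half of cancers, half of benign | 4 / (4 + 3.6) = 4/7.6 = 53% |
| Half of cancers, 70% of benign | 2.4 / (2.4 + 3.6) = 2.4/6.0 = 40% |

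Over the wider range of inputs, with half of the cancers and no benign patients lost:

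| Cancer prevalence | Sensitivity | NPV, all classified | NPV, half of cancers lost |
|---|---|---|---|
| 80% | 75% | 11.2/22.4 = 0.50 | 11.2/16.8 = 0.67 |
| 80% | 92% | 11.2/14.78 = 0.76 | 11.2/12.99 = 0.86 |
| 90% | 75% | 5.6/18.2 = 0.31 | 5.6/11.9 = 0.47 |
| 90% | 92% | 5.6/9.63 = 0.58 | 5.6/7.62 = 0.74 |

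The rise is 0.10 to 0.17, and it depends on keeping every benign patient.

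**Step 3. Sensitivity**

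If the loss is unrelated to the needle result, expected sensitivity does not change. Only the interval widens: the 95% half-width is 1.96 × √(0.85 × 0.15 / n), which is 0.101 for n = 48 and 0.143 for n = 24.

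If the loss depends on the result, sensitivity can move either way. Starting from 75%:

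- 60% of true positives and 30% of false negatives lost: 0.75 × 0.40 = 0.300 and 0.25 × 0.70 = 0.175, so 0.300/0.475 = 0.63.
- 30% and 60% lost: 0.75 × 0.70 = 0.525 and 0.25 × 0.40 = 0.100, so 0.525/0.625 = 0.84.

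**The case against.** The strongest reply is that the protocol nowhere excludes these patients. Section 13 is silent on them, section 15 foresees a clinical element in the reference diagnosis, and the handling of unclassified patients is often left to a statistical analysis plan, which is not at hand. This stands in part: exclusion is a consequence of applying section 10 literally, not something the protocol announces. It does not close the gap, because section 10 itself fixes the reference methods and section 15 adds no rule.

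A reader might infer more, namely that a large share of cancers drops out and that NPV is therefore inflated. The documents do not support this. They give no prevalence, resection or survival figure, and longer follow-up would shrink the unclassified share. The direction for NPV is also open, because some benign patients lose their route too. The wording of the follow-up method adds to this: it can mean neither progression nor regression, or it can mean that regression counts as benign. Under the first meaning, benign lesions that regress also lose their reference. If the inflammation phrase is attached to the imaging modality alone, the benign half of the point weakens; the malignant half does not.

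Two further points stand. Both needles are used in every patient, so a missing reference removes the patient from both needles alike. And the primary goal does not use the reference standard.

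**Conclusion.** The point holds in this form: the listed methods give no malignant diagnosis to an unresected patient alive at follow-up, and no benign diagnosis to an unresected patient whose mass was not suspected inflammation at entry. Applied as written, the rule keeps such patients out of sensitivity, specificity, accuracy and both predictive values.

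The number affected cannot be derived from the protocol; the 28-72% of cancers rests wholly on the assumed resection and death rates. The sure consequence of losing cancers is reduced precision for sensitivity, for example from about ±10 to ±14 points if half of 48 cancers are lost. Inflation of NPV (53% to 69% in the example) requires that cancers be lost more often than benign cases. A bias in sensitivity requires that loss depend on the needle result. Neither condition is established. Only the secondary goal of diagnostic performance is affected, so this should be corrected but does not threaten the primary comparison.

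**What to change.** In section 10:

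- Add a malignant reference route for unresected patients: clinical or imaging progression consistent with malignancy, new metastasis, or malignant tissue from another site or a later routine procedure, during the follow-up already planned.
- Open the follow-up route to every unresected patient, whatever was suspected at entry.
- State whether regression counts as benign.
- Tie these rules to the clinical and pathological reference diagnosis listed in section 15.
- Require that the reference diagnosis be assigned without using the results of the two trial needles.

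In the analysis, report how many patients remain unclassified, and show the accuracy measures with and without the progression-based diagnoses. The rule should be set before diagnoses are assigned, so that it is not chosen with results in view.

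The cost is about one paragraph and one extra table. No new visits are needed, since follow-up is planned; the protocol sets no imaging schedule for it, so imaging evidence would be whatever routine care provides. The downside is small: progression is a less definite reference than resection histology, which is why both sets of results should be shown.

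### The reference standard gives no route to a malignant label for a living, unresected patient, or to a benign label for an unresected lesion first thought malignant

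*Protocol*

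**What the plan says.** Protocol section 10 lists three reference methods for the final benign or malignant diagnosis:

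- (a) "definite benign or malignant pathological diagnosis based on analysis of surgically resected specimens from operated patients";
- (b) death from the disease, with no time window;
- (c) "no signs of disease progression or regression during the 6 month or longer follow-up periods", judged by clinical course or imaging and "used for suspected pancreatic inflammation at the time of the procedure".

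Entry (section 6) is open to "suspected solid pancreatic masses based on clinical work up and image modality that required cytopathological confirmation"; operability is not required. Section 10 also expects patients who do not have surgery: "non-surgical patients received clinical follow-ups for at least 6 months".

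Diagnostic performance is a secondary goal (section 12). Section 13 asks for sensitivity, specificity, accuracy, PPV and NPV, with values up to the "negative predictive value (NPV) of each needle were calculated based on per protocol analysis". Section 15 names a final clinical and pathologic reference diagnosis among the recorded variables but adds no rule for reaching it.

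**The concern.** Every measure in section 13 needs a reference label for each patient. Under section 10 a malignant label can come only from (a) or (b), and (c) is a benign route open only to presumed inflammation. The study therefore enrols and follows patients whom its own reference cannot label. Two responses are possible. One is to leave them out, so that the accuracy measures describe patients selected by operability and survival. The other is to let the biopsy decide its own correctness, which is incorporation bias. Section 3 gives low NPV as a main limitation of existing sampling, so readers will look closely at a measure that depends on this reference.

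**Working it through.** **Step 1: patient types against the three routes.**

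| Patient | (a) | (b) | (c) |
|---|---|---|---|
| Resected, benign or malignant | yes | – | – |
| Unresected cancer, died of it | no | yes | no |
| Unresected cancer, alive and progressing | no | no | no |
| Unresected cancer, alive and stable or shrinking on treatment | no | no | no, unless first suspected as inflammation |
| Unresected, suspected inflammation, stable or regressing | no | no | yes |
| Unresected, suspected malignant, later behaves as benign | no | no | no |

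Rows three, four and six have no proper route. No other section supplies one. This step needs no assumption.

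**Step 2: how many patients could be affected.** The protocol gives no figure for this, so there is none to reproduce. The base is the 56 evaluable pairs of section 5 (56/0.85 = 65.9, hence 66 planned). All other shares are assumptions.

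Malignant cases without a route = 56 × m × (1 − r) × (1 − d), where m is the malignant share, r the resected share of those, and d the share of the unresected who have died of disease by the assessment.

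For m 80–90%, r 15–50% and d 10–40%:

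- lowest: 56 × 0.80 × 0.50 × 0.60 = 13.4;
- highest: 56 × 0.90 × 0.85 × 0.90 = 38.6.

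That is 0.50 × 0.60 = 30% to 0.85 × 0.90 = 77% of malignant cases.

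**Step 3: effect on NPV if only malignant cases are lost.** Assume sensitivity 80% and specificity 100%. With B benign and M malignant patients, NPV = B / (B + 0.2 × M).

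| m | r | d | No route | NPV, all 56 | NPV, classifiable only |
|---|---|---|---|---|---|
| 75% | 25% | 40% | 18.9 | 14/22.4 = 62.5% | 14/(14 + 4.62) = 75.2% |
| 75% | 15% | 20% | 28.6 | 62.5% | 14/(14 + 2.69) = 83.9% |
| 85% | 25% | 40% | 21.4 | 8.4/17.92 = 46.9% | 8.4/(8.4 + 5.24) = 61.6% |
| 85% | 15% | 20% | 32.4 | 46.9% | 8.4/(8.4 + 3.05) = 73.4% |

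**Step 4: effect on NPV if benign cases are lost too.** Step 1 shows that benign lesions first thought malignant also drop out. In the first row of step 3, lose half of the 14 benign cases: NPV = 7/(7 + 4.62) = 60.2%, just below the 62.5% of the full cohort. In general, with equal sensitivity in kept and lost patients, NPV rises only if a larger share of benign than of malignant cases is kept. In that row the malignant share kept is 0.25 + 0.75 × 0.40 = 55%.

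**Step 5: sensitivity and accuracy.** Assume 56 patients, 85% malignant, sensitivity 85%, specificity 100%, and no benign losses. There are then 40.46 true positives, 7.14 false negatives and 8.4 true negatives.

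| True positives lost | False negatives lost | Sensitivity | Accuracy | NPV |
|---|---|---|---|---|
| 0% | 0% | 0.850 | 0.872 | 0.541 |
| 60% | 60% | 0.850 | 0.896 | 0.746 |
| 60% | 10% | 0.716 | 0.793 | 0.567 |
| 30% | 60% | 0.908 | 0.928 | 0.746 |

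Sensitivity and accuracy can move either way, depending on which cancers are lost.

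**The case against.** The strongest reply is that nothing says unclassified patients are left out. Section 15 foresees a reference diagnosis that is partly clinical, and an SAP may say how to handle indeterminate cases. Follow-up has a minimum but no maximum, so later deaths would move some patients into (b). This stands in part: the number affected is unknown and exclusion is an inference. But the protocol itself fixes the list of reference methods, and that list is incomplete whatever is done with those it leaves out.

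Four stronger readings are tempting, and the document supports none of them.

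- **NPV must be inflated.** That follows only if benign cases are all or mostly kept. Step 4 shows that it can fail.
- **Most patients will be unclassifiable.** The protocol gives no malignancy, resection or death shares and no cut-off for (b). The counts are illustrations.
- **The needle comparison is invalid.** Core procurement, the primary goal, needs no reference diagnosis. Each patient receives both needles, so both lose the same patients. The paired comparison loses precision and generalisability rather than balance.
- **Route (c) should simply apply whatever was suspected.** A cancer stable or shrinking on treatment would then be labelled benign, and a correct positive biopsy would count as a false positive. The restriction to suspected inflammation guards against this.

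The wording of (c) could also be read as excluding a regressing lesion. Its evident sense is stable or regressing, so this calls only for clearer wording.

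**Conclusion.** The gap is real and follows from the text of section 10 alone: two kinds of patient that the study will admit and follow cannot receive a reference diagnosis. If they are omitted, sensitivity, accuracy and NPV, and possibly specificity and PPV, describe a subset selected by operability and survival. If the biopsy fills the gap, those measures are partly circular. The illustrative range is 13 to 39 of 56 patients, from malignant cases alone, and it rests wholly on assumed shares. No direction of bias is established for any measure. Only a secondary goal is affected; the primary endpoint and its sample size are not. This is a should-fix point.

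**What to change.** Amend the reference standard in section 10:

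1. Add a route (d): malignant if a non-operated patient has a clinical course or imaging over 6 months or more of follow-up that is consistent with malignancy. Judge this without reference to which needle gave which result, and not on the evaluated needle's result alone.
2. Clarify (c) so that stable or regressing lesions count as benign only in the absence of anticancer treatment.
3. Report any remaining patients as undetermined, with their number, and add a sensitivity analysis that classifies them all as malignant and then all as benign.

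The cost is mainly wording. Section 10 already provides at least 6 months of clinical follow-up for non-surgical patients, and (c) already accepts clinical course or imaging. The protocol sets no schedule for follow-up imaging, so (d) should accept either source and not depend on scans that may not exist. The downside is that a clinical reference is less certain than surgical pathology, so results should show how many patients were classified by each route.
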